***Interviewer:***

→ Now I’m going to ask you a few questions about what members of your camp think about HIV. In response to each question, please let me know if you think no one, very few people, some people, or most people in the camp believe it to be true.

| **No.** | **Questions and Filters** | **Coding Categories** | **Codes** | **Skip to:** | **VARIABLE** |
| --- | --- | --- | --- | --- | --- |
| Q901 | In your camp, how many people think that people with HIV have brought shame on their families? | NO ONE  VERY FEW PEOPLE  SOME PEOPLE  MOST PEOPLE | 1  2  3  4 |  | CMPSTIG1 |
| Q902 | In your camp, how many people would avoid visiting the homes of people with HIV? | NO ONE  VERY FEW PEOPLE  SOME PEOPLE  MOST PEOPLE | 1  2  3  4 |  | CMPSTIG2 |
| Q903 | In your camp, how many people think that if you have HIV you have done wrong behaviors? | NO ONE  VERY FEW PEOPLE  SOME PEOPLE  MOST PEOPLE | 1  2  3  4 |  | CMPSTIG3 |

Section 10: Alcohol and Drug Use

***Interviewer:***

→ Now I’d like to ask you some questions about your drinking habits and substance use. I know that these are sensitive questions and want to remind you that your responses are confidential.

| **No.** | **Questions and Filters** | **Coding Categories** | **Codes** | **Skip to:** | **VARIABLE** |
| --- | --- | --- | --- | --- | --- |
| Q1001 | Have you ever used alcohol **in your lifetime?** | NO  YES | 0  1 | **Q1005** | ALC_EVR |
| Q1002 | **In the past month**, how often did you use any alcohol? If you don’t know exactly, give a best guess. | NEVER  LESS THAN ONCE A WEEK  1-3 TIMES A WEEK  >3 TIMES A WEEK | 0  1  2  3 | **Q1005** | ALC_FRQ |
| Q1003 | **In the past month**, how often, on average did you drink until you were intoxicated? If you don't know exactly give a best guess. | NEVER  LESS THAN ONCE A WEEK  1-3 TIMES A WEEK  >3 TIMES A WEEK | 0  1  2  3 | **Q1005** | DRNK_FRQ |
| Q1004 | **In the past month,** have you had 5 drinks or more during any one given occasion?  Probe: One drink equals one beer, one glass of wine, or one ounce of hard alcohol | NO  YES | 0  1 |  | ALC_BING |
| Q1005 | Have you ever used marijuana in your lifetime? | NO  YES | 0  1 | **Q1007** | MRJ_EVR |
| Q1006 | How often did you smoke marijuana in the last 12 months? | NOT AT ALL  EVERY DAY  A FEW TIMES A WEEK  ONCE OR TWICE A MONTH  ONCE EVERY FEW MONTHS | 0  1  2  3  4 |  | MRJ_FRQ |
| Q1007 | Have you ever smoked a “cocktail” (mixture of heroin and marijuana) in your lifetime? (I want to remind you that your response will be confidential) | NO  YES | 0  1 | **Q1009** | CKT_EVR |
| Q1008 | How often have you smoked “cocktails” in the last 12 months? | NOT AT ALL  EVERY DAY  A FEW TIMES A WEEK  ONCE OR TWICE A MONTH  ONCE EVERY FEW MONTHS | 0  1  2  3  4 |  | CKT_FRQ |
| Q1009 | Have you ever injected heroin, opium, or cocaine? | NO  YES | 0  1 |  | HINJ_EVR |

Section 11: Social Support

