## 3.3 Study Duration and Endpoints

The intervention will be implemented for two years, and the total duration of the trial will be 5 years. **The primary endpoints** are sexually transmitted infections including Neisseria gonorrhea (NG), Trichomonas vaginalis (TV), Chlamydia trachomatis (CT), and perpetration of physical or sexual violence against a sexual partner. A random sample of 50% of participating men will be flagged for an STI test at baseline to assess relative prevalence, and all men will be tested at endline. A test of relative prevalence at baseline will aid in establishing equivalency in the two arms; any lack of equivalency then will be controlled for appropriately at endline. All participants will complete a behavioral assessment at baseline, 12 months and 30 months to assess secondary objectives. **Secondary endpoints** are HIV risk and protective behaviors including: gender equity, alcohol and drug use, sexual relations and risk behavior, uptake of HIV counseling and testing; unprotected sexual intercourse; consistent condom use; delay of sexual debut; number of sexual partners, and sexual concurrency. **Key mediators** are hope, future orientation, social cohesion, collective efficacy, emotional distress, sexual networks, social support and social influence.

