**Alcohol and Drug Use**

Participants will be asked about lifetime use of alcohol and drugs. Participants who have used alcohol will be asked about use in the last month, frequency of use, frequency of use until intoxication, and if consumed greater than 5 drinks in one sitting. Participants who have used drugs will be asked about use and frequency of use in the last 12 months.

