**Behavioral Survey**

An approximately 1 hour behavioral survey instrument will be created and formatted in Samsung Galaxy tablets. The survey will be comprised of variables that assess, but are not limited to, demographic data, HIV risk and protective behaviors, social and sexual networks, gender-based violence perpetration and victimization, hope, collective efficacy, emotional distress, social support, alcohol and drug use, and work and expenditures. The behavioral survey form will be used at baseline, and 12 and 30 month follow-ups.

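### Appendix D does not ask the five-drinks item (Q1004) of past-month drinkers who report no intoxication, so recorded heavy drinking can only be a subset of self-reported intoxication

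*Protocol*

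**What the plan says.** Appendix D, Section 10 runs as follows.

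- Q1001: lifetime alcohol use, with a skip to Q1005.
- Q1002: frequency of use in the past month, coded from NEVER (0) to more than three times a week (3), with a skip to Q1005.
- Q1003: "how often, on average did you drink until you were intoxicated" in the past month, on the same four codes, again with a skip to Q1005.
- Q1004 (ALC_BING): "have you had 5 drinks or more during any one given occasion" in the past month, answered no or yes.
- Q1005: "Have you ever used marijuana in your lifetime".

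Section 7.4.1, under Alcohol and Drug Use, describes the same content: "Participants who have used alcohol will be asked about use in the last month, frequency of use, frequency of use until intoxication", and then "if consumed greater than 5 drinks in one sitting". It mentions no intoxication filter.

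Section 3.3 defines the secondary endpoints as "HIV risk and protective behaviors including: gender equity, alcohol and drug use" and further behaviours. Section 9.1.4 also lists alcohol and drug use among the mediators. Section 8.2.3 states: "The behavioral survey form will be used at baseline, and 12 and 30 month follow-ups".

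**The concern.** The skips at Q1001 and Q1002 do no harm: a man who drank no alcohol in the past month cannot have had five drinks on one occasion in that month. The skip at Q1003 is different. Not having felt intoxicated does not imply not having had five drinks, yet the form treats the first as settling the second.

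The answer is then never collected, so no later analysis can rebuild it. The recorded item also depends on how a man perceives or reports drunkenness as well as on how much he drank. Section 7.4.1 and the form further disagree on the cut-off: a man whose largest occasion was exactly five drinks is positive on the form and negative under Section 7.4.1.

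**Working it through.** The plan gives no figure for this item, so there is nothing to reproduce. The check has two parts.

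**1. Routing.** The printed table does not tie the Q1003 skip to a particular code. If it fired for every answer, Q1004 could never be reached. Q1001 and Q1002 carry the same target, which makes sense only for their zero answers. NEVER (0) is therefore the coherent reading. The possible paths are:

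| Ever drank | Past-month drinking | Any reported intoxication | Had 5+ drinks | Q1004 | Recorded |
|---|---|---|---|---|---|
| no | no | no | no | skipped | blank or 0, correct |
| yes | no | no | no | skipped | blank or 0, correct |
| yes | yes | no | no | skipped | blank or 0, correct only by luck |
| yes | yes | no | yes | skipped | **blank or 0, lost** |
| yes | yes | yes | no | asked | 0 |
| yes | yes | yes | yes | asked | 1 |

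A value of 1 can arise only when Q1003 is at least 1. Rows 3 and 4 cannot be told apart in the data.

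**2. Size, under assumption.** Let p be the prevalence of five or more drinks that would be reported if every past-month drinker were asked. Let s be the share of those men who report any intoxication at Q1003. With skipped men coded 0, recorded prevalence = p × s. The documents give neither p nor s, so all values below are assumed.

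| p | s = 0.9 | s = 0.8 | s = 0.7 | s = 0.5 |
|---|---|---|---|---|
| 10% | 9% | 8% | 7% | 5% |
| 20% | 18% | 16% | 14% | 10% |
| 30% | 27% | 24% | 21% | 15% |

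If s is the same in both arms, the odds ratio moves little. Take an assumed true odds ratio of 0.65, control p = 20% and s = 0.8. The intervention odds are 0.25 × 0.65 = 0.1625, so p = 0.1398. The recorded values are 0.1118 and 0.16, giving (0.1118/0.8882)/(0.16/0.84) = 0.661.

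If s differs by arm, a ratio appears with no true difference. At p = 20% in both arms and s = 0.8 in control:

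- s = 0.7 in intervention: (0.14/0.86)/(0.16/0.84) = 0.855
- s = 0.9 in intervention: (0.18/0.82)/(0.16/0.84) = 1.152

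The direction therefore depends entirely on an unknown.

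**The case against.** Four objections deserve an answer.

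**Section 7.4.1 summarises content; it does not specify routing.** This stands. A reader might infer that the section promises the heavy-drinking question to all men who have ever used alcohol. It does not say all, and read that literally it would also conflict with the harmless Q1002 skip. What remains is that it lists the items side by side with no intoxication condition, and that its threshold differs from the form's.

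**The purpose of Q1004 is not stated.** This also stands. A reader might infer that the item was included as a count independent of perceived drunkenness. That would be sound measurement practice, but the protocol does not say so, and the form is also consistent with a follow-up question among men reporting intoxication.

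**Between-arm bias is not shown.** A reader might infer it from the alcohol sessions on Day 2 of the leader training (Appendix C), since under Section 5.4 control camps receive only an HIV session, after the 30-month data collection. That is a possible mechanism, not evidence. Both arms answer the same form, any difference in s is assumed and could go either way, and Q1004 is itself sensitive self-report, so removing the skip need not remove differential reporting.

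**Changing the form midway has a cost.** The note at Q004 treats anyone born after the interview date in 1998 as under 15, which dates the form to about 1998 + 15 = 2013; protocol version 2.0 is dated September 2015. Baseline may already have been collected with the skip, and Section 8.2.3 plans one form for all waves. This stands, and the fix must cover it.

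**Conclusion.** The point holds as a limited instrument defect. On the only workable reading of the skip, heavy drinking as recorded is by construction contained within self-reported intoxication. With skipped men coded 0, it equals or understates the prevalence that would have been reported. It is strictly an undercount only if some men had five or more drinks without reporting intoxication. That is plausible, but the documents do not quantify it. Neither the size nor any difference between arms can be determined from them; the figures above show what assumed values would imply.

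It would go too far to conclude that the alcohol endpoint as a whole is undercounted. No passage makes ALC_BING the endpoint on its own. Q1002, Q1003, the drug items and both primary endpoints are untouched. The threshold mismatch is a separate wording inconsistency that needs its own correction. The change is worth making because it is cheap and the lost answers cannot be recovered later, not because it threatens the trial's main conclusions.

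**What to change.** - Remove the skip to Q1005 at Q1003, so that every past-month drinker (Q1002 at least 1) answers Q1004. Keep the skips at Q1001 and Q1002.
- Use one threshold in Section 7.4.1 and in the form. If a wave has already been collected, its yes/no answers at five or more cannot be converted to more than five, which favours the form's wording for comparability.
- For any wave collected with the skip, set ALC_BING to missing, not 0, for past-month drinkers who answered NEVER at Q1003. That wave holds no observed answer for this group, so imputation from it alone rests wholly on assumption. Coding the whole group 0 and then 1 gives bounds.
- Compare waves with and without the skip on the old definition, restricted to men with Q1003 at least 1. This can be rebuilt from the corrected form.

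The cost is one routing edit, a few seconds per interview, one wording correction and one extra derived variable.

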***Interviewer:***

→ Now I would like to ask some questions about the support you may be getting from your friends and family.

| **No.** | | **Questions and Filters** | **Coding Categories** | **Codes** | **Skip to:** | **VARIABLE** |
| --- | --- | --- | --- | --- | --- | --- |
| Q1101 | | In the last 12 months, were the following individuals available for you to talk to?  MOTHER  FATHER  SISTERS, AUNTS, OTHER FEMALE RELATIVES  BROTHERS, UNCLES, OTHER MALE RELATIVES  SEXUAL PARTNER  CAMP MEMBERS  OTHER CLOSE FRIENDS OUTSIDE OF THE CAMP  OTHER________________________ | NO  YES | 0  1 | **For each category, if participant indicates “NO”, do not ask follow-up questions (Q1102-Q1104) for that category.** | SSAVLM  SSAVLF  SSAVLFF  SSAVLMF  SSAVLSP  SSAVLCM  SSAVLCF  SSAVLO  SSAVLO_S |
| Q1102 | | In the last 12 months, have you talked about a personal problem with any of the following people?  MOTHER  FATHER  SISTERS, AUNTS, OTHER FEMALE RELATIVES  BROTHERS, UNCLES, OTHER MALE RELATIVES  SEXUAL PARTNER  CAMP MEMBERS  OTHER CLOSE FRIENDS OUTSIDE OF THE CAMP  OTHER________________________ | NO  YES | 0  1 |  | SSTLKM  SSTLKF  SSTLKFF  SSTLKMF  SSTLKSP  SSTLKCM  SSTLKCF  SSTLKO |
| Q1103 | | In the last 12 months, have you talked to any of the following individuals about HIV?  MOTHER  FATHER  SISTERS, AUNTS, OTHER FEMALE RELATIVES  BROTHERS, UNCLES, OTHER MALE RELATIVES  SEXUAL PARTNER  CAMP MEMBERS  OTHER CLOSE FRIENDS OUTSIDE OF THE CAMP  OTHER________________________ | NO  YES | 0  1 |  | SSHIVM  SSHIVF  SSHIVFF  SSHIVMF  SSHIVSP  SSHIVCM  SSHIVCF  SSHIVO |
| Q1104 | In the last 12 months, have you received money or other things you needed from any of the following people?  MOTHER  FATHER  SISTERS, AUNTS, OTHER FEMALE RELATIVES  BROTHERS, UNCLES, OTHER MALE RELATIVES  SEXUAL PARTNER  CAMP MEMBERS  OTHER CLOSE FRIENDS OUTSIDE OF THE CAMP  OTHER________________________ | | NO  YES | 0  1 |  | SSMONM  SSMONF  SSMONFF  SSMONMF  SSMONSP  SSMONCM  SSMONCF  SSMONO |

Section 12: Social Network

­­­­­­­­

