### 5.3.3 Implementation of Strategies with Camps

Once trained, leaders will be asked to implement the communication and social influence strategies they learned within their camps. Leaders will record information about the number of times they engage in peer discussions about the issues discussed in training, the topics, the sex of their discussant, and any challenges encountered. See Process Evaluation in Section 7.8.

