**Perceived Social Support**

We will use the Adolescent Perceived Microsystems Scale for Social Support to assess emotional and material support ([Seidman et al., 1995](#_ENREF_81)) This scale, including a measure of support for sexual health information, demonstrated high reliability among youth in rural Kenya (α = .95).([Puffer et al., 2010](#_ENREF_69)) This study ranked received support on a 4-point Likert scale. For our study participants will answer Yes or No regarding support they receive from family members, relatives, peers and sexual partners.

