### 9.1.4 Mediation Sampling and Analytical Technique

In the event that program effects are identified, we will estimate path coefficients in multiple mediator models and generate bootstrapped confidence intervals for total and specific indirect effects of one or more mediator models using the Mplus program Version 6.11.([Pituch, Stapleton, & Kang, 2006](#_ENREF_65)) We will assess simple and multiple mediation in the relationships between the microfinance intervention condition, intervention mediators including hope, future orientation, social cohesion, social support, emotional distress, gender equity, conflict, alcohol and drug use, HIV stigma, perceived social support, collective efficacy, sexual relationships and risk behavior, attitudes towards HIV risk and intimate partner violence, work and expenditures, sexual relationships and risk behavior, and social and sexual network norms.

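### The survey skips the money-or-goods question for anyone the man says was not available to talk, so material support from those sources is never recorded

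*Protocol*

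**What the plan says.** Protocol section 7.4.1, under Perceived Social Support, says the scale is used "to assess emotional and material support" and that "participants will answer Yes or No regarding support they receive from family members, relatives, peers and sexual partners". It mentions no filter on which sources are asked about.

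Appendix D, Section 11, is the instrument. Q1101 is the opening question: "In the last 12 months, were the following individuals available for you to talk to". It is answered for eight categories: mother, father, female relatives, male relatives, sexual partner, camp members, other close friends, and other. For each category answered NO, the routing note says "do not ask follow-up questions (Q1102-Q1104) for that category". Three items fall in that range:

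- Q1102: talked about a personal problem.
- Q1103: talked about HIV.
- Q1104: "In the last 12 months, have you received money or other things you needed from any of the following people".

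Social support is a named mediator in the Protocol Summary and in sections 2.3, 3.3 and 9.1.4. Section 9.1.4 lists "intervention mediators including hope, future orientation, social cohesion, social support, emotional distress" among others.

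**The concern.** Being available to talk is a condition for emotional support. It is not a condition for giving money or goods: a father or an uncle may send money without being someone the man can talk to. The routing treats the first as a precondition for the second, so the form does not measure what section 7.4.1 says it measures.

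The loss cannot be repaired in analysis, because the answer was never collected. A YES on Q1104 also implies a YES on Q1101 by construction, so the data cannot show material support acting apart from availability to talk.

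There is a second, conditional risk. Camp members are one of the gated categories, and the intervention works through talk within camps. If it changes how often men call camp members available, it also changes how often Q1104 is asked about them. Recorded material support could then differ between arms without any difference in what men received.

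**Working it through.** **The routing, item by item**

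| Item | Does a NO on Q1101 make it redundant? |
|---|---|
| Q1102, talked about a personal problem | Largely yes: same source, same 12 months |
| Q1103, talked about HIV | Largely yes, for the same reason |
| Q1104, received money or goods | No: giving does not require talking |

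Other items in Appendix D touch on money but do not replace Q1104. Q501 asks how often camp members do each other favours, Q1515 is about money for sex, and Q1615 covers business start-up capital only.

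**Size of the undercount.** The documents state no rates, so there is no figure to reproduce, and every rate below is an assumption. For one source, let *a* be the proportion of men saying it was available, *r1* the proportion receiving from it when available, and *r0* when not.

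- True proportion = *a·r1* + (1 − *a*)*·r0*
- Recorded proportion, skipped items scored 'no' = *a·r1*
- Undercount = (1 − *a*)*·r0*

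With *r0* = 40%, the undercount is 0.40 × 0.40 = 16 points at *a* = 60%, 0.20 × 0.40 = 8 points at 80%, and 0.05 × 0.40 = 2 points at 95%. With *r0* = 20% these halve to 8, 4 and 1 points. With *r0* = 0 there is no loss.

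**Possible difference between arms (camp members).** Suppose the intervention raises availability from *aC* to *aI* and changes nobody's actual receipt. True receipt is then *aC·r1* + (1 − *aC*)*·r0* in both arms. With skipped items scored 'no':

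- Recorded, control = *aC·r1*
- Recorded, intervention = *aC·r1* + (*aI* − *aC*)*·r0*

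With skipped items set to missing, the rate among men asked is *r1* in control and the recorded intervention figure divided by *aI* in intervention. Throughout, *r1* = 40%.

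| *r0* | Availability, control vs intervention | Skipped = 'no' | OR | Skipped = missing |
|---|---|---|---|---|
| 40% | 60% vs 80% | 24% vs 32% | 1.49 | 40% vs 40% |
| 40% | 80% vs 90% | 32% vs 36% | 1.20 | 40% vs 40% |
| 40% | 95% vs 98% | 38.0% vs 39.2% | 1.05 | 40% vs 40% |
| 20% | 60% vs 80% | 24% vs 28% | 1.23 | 40% vs 35% |
| 20% | 95% vs 98% | 38.0% vs 38.6% | 1.03 | 40% vs 39.4% |
| 0% | 60% vs 80% | 24% vs 24% | 1.00 | 40% vs 30% |

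Worked example, first row: recorded intervention = 0.60 × 0.40 + 0.20 × 0.40 = 0.32, and OR = (0.32/0.68) ÷ (0.24/0.76) = 1.49.

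So the artefact can favour the intervention arm, be absent, or run the other way, depending on scoring and on *r0*. Setting skips to missing does not recover the true rate either. In the fourth row true receipt is 0.60 × 0.40 + 0.40 × 0.20 = 32% in both arms, while the men asked show 40% and 35%.

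**The case against.** The strongest objection is to the stronger reading a reader might infer: that the health leaders make camp members available to talk, so material support will appear to rise in the intervention arm and create a false mediation path. The documents do not support that as a finding, for four reasons.

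- The direction requires skipped items to be scored 'no'. The Protocol states no scoring rule, and such a rule may properly sit in the statistical analysis plan.
- Availability of camp members may be near ceiling. Section 4.3.1 requires at least weekly visits (enforced at Q007) and three months' membership. Section 1.7 reports that 73% of men in the earlier study socialized in their camp daily. Q1101 also asks about camp members as a group over 12 months.
- Section 5.3.3 says "leaders will be asked to implement the communication and social influence strategies they learned within their camps". It does not say that camp members become more available to talk in general, which is what Q1101 asks.
- The analysis is conditional. Section 9.1.4 runs mediation only if program effects are found, social support is one of many listed mediators, and the Protocol defines no separate material-support score.

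A reader might also infer that Q1103 is mis-measured by the same skip. It is not: someone not available to talk in the last 12 months could hardly have been talked to about HIV in that period.

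These points limit the arm-bias argument. They do not touch the undercount, which follows from the routing alone and is most plausible for parents and relatives.

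A fair practical objection is timing. The age check at Q004 uses a 1998 birth year for age 15, which places the form at about 2013, while the revision history runs to September 2015. Baseline may already have been collected with the skip in place. Section 8.2.3 says the form is used at all three waves, but section 7.4.1 adds moral agency questions at midpoint and endpoint that Appendix D does not list. The routing actually used at follow-up is therefore not shown.

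**Conclusion.** The point holds for Q1104 only. As written, money or goods from a source not available to talk are never recorded, although section 7.4.1 says material support is measured. The number of sources recorded as giving can only be too low, and material support cannot be told apart from availability to talk.

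The size cannot be fixed from the documents. Under the assumed rates above, the undercount for a source runs from 0 to 16 points, depending on how many men call it unavailable and how many of those receive from it anyway.

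An artefactual difference between arms is possible, not established. It needs an arm difference in camp members' availability, and its direction depends on how skips are scored: with skips scored 'no' the illustrative OR runs from 1.00 to 1.49, and near-ceiling availability gives 1.03 to 1.05. With skips set to missing it is nil or reversed.

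Severity is minor: one component of a mediator is affected, and no primary endpoint.

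**What to change.** Change the routing in Appendix D, Section 11, so that Q1104 is asked for every category whatever the answer to Q1101. Keep the skip for Q1102 and Q1103. For comparison with any wave already collected, also derive the gated score, that is, Q1104 restricted to categories with Q1101 = YES.

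With Q1104 ungated, the artefact goes: true receipt of 40% in both arms is recorded as 40% vs 40% (OR 1.00) whatever the arms' availability.

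The cost is a change to the CAPI routing and up to eight extra yes/no answers per interview. The ungated score will not be directly comparable with waves already collected under the skip, which is why the gated score should be kept alongside it.
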